### Sample size justification

To obtain the confidence interval with the width of 1 standard deviation (SD), which has a 90% chance to include the true difference of mean change in neuropsychological test score at three months between the intervention and control groups, requires 22 participants in each group. By considering the 25% drop-out rate, 30 participants will be required in each group. Thus, the total sample size will be 90 participants (30 in the AT intervention group, 30 in MRA, and 30 in the control group).

### Assessments and visit schedule

#### Pre-baseline

Screening, consent taking, and eligibility criteria are checked. Those with high GDS/GAI scores will go through a SCID examination to evaluate the presence of a major psychiatric disorder. This will be done by psychiatrists in the study team who have been trained to do this examination. Any participants found to have a psychiatric disorder through the SCID examination will be referred for follow-up by a medical professional. A standard referral letter has been prepared.

#### Baseline

Demography questionnaire, basic health screen, functional assessment, neuropsychological tests, neuroimaging, and blood investigations are carried out.

#### Three months

Basic health screen (excluding height), functional assessment, neuropsychological tests, neuroimaging, and blood investigations are repeated.

#### Nine months (study end)

Basic health screen (excluding height), functional assessment, neuropsychological tests, and blood investigations are repeated.

The time taken for the health screening, completion of the demographic data, main questionnaire, and blood sample collection will take about 1 h.

The neuropsychological tests will take about 1 h 45 min. The baseline visit to TaRA@JP will take about 3 h. Subsequent visits at three months and nine months will take 2 h.

The fMRI scans will be conducted at CIRC in NUS and the appointment will be on another day. The imaging sessions will take 1 h. However, the time within the scanner is about 45 min.

See Tables 1 and 2 for the visit schedules for the interventions and control groups, respectively.

**Table 1 Tab1:** Visit schedule for intervention arms

Pre-baseline/Baseline	Three months	Nine months (study end)
Informed consent process	Main questionnaire	Main questionnaire
Eligibility screening	Neuropsychological tests	Neuropsychological tests
Demographic data	MRI scan	Clinical Dementia Rating
Main questionnaire	Weight, vital Signs	Weight, vital signs
Neuropsychological tests	Blood sample collection	Blood sample collection
Clinical Dementia Rating		
MRI scan		
Basic health screen		
Blood sample collection

**Table 2 Tab2:** Visit schedule for controls

Pre-baseline/Baseline	Three months	Nine months (study end)
Informed consent process	Main questionnaire	Main questionnaire
Eligibility screening	Neuropsychological tests	Neuropsychological tests
Main questionnaire	MRI scan	Clinical Dementia Rating
Demographic data	Weight, vital signs	Weight, vital signs
Neuropsychological tests		Blood sample collection
Clinical Dementia Rating		
MRI scan		
Basic health screen		
Blood sample collection		

Blood samples (3 mL) will be collected at three time-points for those in the AT and MRA arms (baseline, three months, nine months) for telomere lengths. For the control group, it will be done twice, at baseline and at nine months.

Samples will be stored immediately in a mini-fridge (4 °C) at TaRA@JP and transported within 12 h of collection to the labs.

### Risks and safety monitoring

Risks include some pain and bruising during blood sampling. To minimize risks associated with the blood, sampling only one venipuncture will be performed at each of the three time-points and blood will be collected using vacutainers. Trained nurses will perform the procedure.

Some may experience some discomfort from the noise and the enclosed space within the scanner. Participants will be informed about the noise and ear plugs will be provided. If the noise is intolerable and the participant wishes to discontinue with the scanning, the scanning will be stopped.

### Data management

Data forms will be coded with a study number (starting with 001). Data will be entered and stored on a standalone computer and the information will be password protected. Only the principal investigator, investigators, and study coordinator in the project will have access to the data for analysis. In accordance with NUS data management policy (DPRT-2011-04), data will be kept for ten years after the research is completed and all data (electronic and hard copy) will be destroyed after the storage period.

The investigators and the trial coordinators will monitor that the informed consent process is conducted appropriately and that informed consent was obtained prior to proceeding with any study procedures. Only participants who meet study eligibility criteria will be enrolled.

Participants’ data will be identified only by a study number. Only the principal investigator will have access to identifiers that can link the data to the individual participant. De-identified data will be collected and analyzed as specified in the protocol. Participants who drop out will be noted and their reasons documented. Primary and secondary end-points will be reviewed to ensure data are correctly entered and meet protocol requirements.

### Statistical analyses

All efficacy analyses will be carried out on an intention-to-treat (ITT) basis. That is, all randomized participants will be included in the analysis and the intervention group of participants will be according to the randomization list planned prior to the intervention commencement.

The primary outcomes – neuropsychological test scores – at baseline, three months, and nine months will be modeled using the linear mixed model for repeated measurements. Differences in the estimated means of the changes at three and nine months from baseline between the intervention and control groups and their associated 90% and 95% confidence intervals will be calculated. Further, analysis may be performed to adjust the model for potential confounders, such as age, gender, and education level. Secondary outcomes (cerebral functioning, the GDS and GAI scores, and telomere lengths) will be analyzed similar to the primary outcomes.

Demographic and other baseline characteristics and reported adverse events and serious adverse events will be summarized using descriptive statistics.

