### Randomization procedure

Participants will be randomized (on the same day after taking written informed consent, screening, and completing baseline measures) to the AT, MRA, or control groups at a 1:1:1 allocation ratio. Balanced intervention assignments will be achieved using permuted block randomization stratified by gender. Block size will be determined by the statistician responsible for generating the randomization list and will not be made known to the clinical investigator or site personnel.

Implementation of the randomization process will be carried out via a web-based randomization system by Singapore Clinical Research Institute. The randomization system will then determine the intervention arm and provide a unique participation number to be used for the participant.

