### Art therapy

The AT activity was developed by the team in consultation with art therapists. It will have two components: creation of art pieces; and viewing and discussing art pieces with narration of thoughts and inner experiences. Studies have shown that visual art production interventions and cognitive art evaluation groups benefit the individual but in slightly different ways [27]. Hence, this study will include both activities and consider them as one intervention.

The guided viewing and making of visual images and talk therapy with an art therapist contributes to externalization of thoughts and feelings which may otherwise remain unexpressed. Each weekly session will begin with mindful relaxation to help the participants focus on the task ahead. They will be asked to draw anything they want or what they think is relevant to the topic for each session. They will then be asked to share about the picture they have created, feelings, and perspectives, first in pairs and then with the group where image appreciation activities will be used to help participants gain insights and discuss their feelings.

In addition, participants will visit both the National Art Gallery and the National University of Singapore Art Museum once a month in the first three months. They will view displayed artworks in guided sessions and will be invited to share their views and feelings about the artefacts. Each of the AT sessions will last 1 h (inclusive of 5 min of mindful relaxation and a 15-min break). From the fourth to ninth month, fortnightly AT sessions are provided with sessions at the study center alternating with sessions at the National Art Gallery or National University of Singapore Art Museum. Participants will visit the Art Gallery and Art Museum, first, because the art pieces cannot be removed from these places and brought to the research center; second, two sites are involved because neither one of the sites has sufficient docents to manage the number of visits alone. With two sites, each site will host the participants’ visit only once a month in the first three months and then in alternate months for the next six months. Participants will be taken to the Art Gallery and Museum by coach and will be accompanied by research staff during the 15-min journey.

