### Music reminiscence activity

Reminiscence therapy with music entails listening and discussing activities, events, and experiences related to the music. Sessions will be presented as music videos, with additional prompts in the form of photographs, to facilitate therapy. Participants who agree will be asked to bring 10–20 photographs and also choose songs or music for the videos. Reminiscence provokes shared feelings and boosts self-esteem while the group process provides validation for each member [28]. The structured activity was previously planned by the team and used effectively in the earlier naturalistic study [11]. Participants will meet weekly for the first three months and then fortnightly for six months. As in the AT intervention group, each session will begin with a 5-min mindful relaxation and the 1-h session will include a 15-min break.

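### AT and MRA are delivered in interacting groups, but the precision calculation assumes independent participants; if outcomes correlate within session groups, the intervals under-cover and the 1 SD width is not assured

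*Protocol article*

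**What the plan says.** Participants are randomized individually "to the AT, MRA, or control groups at a 1:1:1 allocation ratio" (Randomization procedure).

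Both active arms work through the group. In AT, participants share their pictures "first in pairs and then with the group where image appreciation activities will be used" (Art therapy). In MRA, the protocol says that "the group process provides validation for each member" (Music reminiscence activity). Each programme lists 24 sessions, of which the 12 weekly ones fall in the first three months. The control arm receives no intervention (Control group).

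The sample size is set on precision: a "confidence interval with the width of 1 standard deviation (SD), which has a 90% chance to include the true difference" in mean change at three months between intervention and control. This "requires 22 participants in each group". Then "By considering the 25% drop-out rate, 30 participants will be required in each group", and "the total sample size will be 90 participants" (Sample size justification). No group size, number of groups, ICC or design effect is given.

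The primary neuropsychological outcomes "will be modeled using the linear mixed model for repeated measurements" (Statistical analyses). The differences in change between intervention and control are to be reported with 90% and 95% intervals. The only further adjustment named is for potential confounders such as age, gender and education level.

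**The concern.** This is a partially nested design: individuals are randomized, then two of the three arms are treated in groups. People who meet in the same group, discuss the same material and hear each other's accounts may end up with correlated outcomes. If so, the mean of an active arm is more variable than the same number of independent people would make it.

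A repeated-measures model handles correlation between one person's visits. Unless a group term is added, it does not handle correlation between people in the same session group. Intervals that ignore a positive correlation are too narrow for their nominal level.

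The width of this interval is also the only stated justification for 90 participants, so an unstated independence assumption bears directly on the sample size.

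**Working it through.** **Inputs from the protocol.** 90% two-sided interval, full width 1 SD (half-width 0.5 SD); 22 evaluable per group; 25% drop-out; 30 enrolled per group; three groups.

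**Inputs assumed, because the documents do not give them.** Number of evaluable members per session group, m; ICC of the outcome within session groups; the same total SD in every arm.

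**1. Reproduce the plan's figure under independence.**
- n per group = 2 × (1.645 / 0.5)² = 21.64, rounded up to 22.
- Enrolled: 22 / (1 − 0.25) = 29.3, rounded up to 30. Total 3 × 30 = 90.
- Width at 22 per group = 2 × 1.645 × √(2/22) = 0.992 SD.

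All three figures reproduce, so they contain no clustering allowance.

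**2. Allow for clustering in the active arm only.**
- Design effect DE = 1 + (m − 1) × ICC.
- The variance of the active-versus-control contrast is inflated by (1 + DE)/2, not by DE, because controls are ungrouped. The SE ratio is r = √((1 + DE)/2).
- True width = 2 × 1.645 × √((1 + DE)/n).
- Actual coverage of a nominal 95% interval that ignores clustering = 2Φ(1.96/r) − 1. For a nominal 90% interval, use 1.645.

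**3. Slack.** At n = 22 the width exceeds 1 SD once DE passes 22/(2 × 1.645)² − 1 = 1.03. With groups of 10 that is an ICC of about 0.004. At n = 30 the limit is 30/(2 × 1.645)² − 1 = 1.77.

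**4. Results.**

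| Evaluable per arm | Groups in active arm | ICC | DE | True 90% width (SD) | Coverage of nominal 90% | Coverage of nominal 95% |
|---|---|---|---|---|---|---|
| 22 | any | 0 | 1.00 | 0.99 | 90% | 95% |
| 22 | 2 of 11 | 0.02 | 1.20 | 1.04 | 88% | 94% |
| 22 | 2 of 11 | 0.05 | 1.50 | 1.11 | 86% | 92% |
| 22 | 2 of 11 | 0.10 | 2.00 | 1.21 | 82% | 89% |
| 22 | 1 of 22 | 0.02 | 1.42 | 1.09 | 87% | 93% |
| 22 | 1 of 22 | 0.05 | 2.05 | 1.22 | 82% | 89% |
| 22 | 1 of 22 | 0.10 | 3.10 | 1.42 | 75% | 83% |
| 30 | 2 of 15 | 0.02 | 1.28 | 0.91 | 88% | 93% |
| 30 | 2 of 15 | 0.05 | 1.70 | 0.99 | 84% | 91% |
| 30 | 2 of 15 | 0.10 | 2.40 | 1.11 | 79% | 87% |

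At the mild end, groups of 5 with ICC 0.01 give DE 1.04, width 1.00 SD and 89.7% coverage of a nominal 90% interval, which is negligible.

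**5. What estimating the group variance would cost.** Take two groups of 11 and a group variance estimated from the data. Satterthwaite df = (DE + 1)² / (DE²/k + 1/21), where k is the between-group df: 1 from one active arm, 2 if AT and MRA are pooled.
- ICC 0.05, k = 1: 6.25 / (2.25 + 0.048) = 2.7 df, t = 2.46, width = 2 × 2.46 × √(2.5/22) = 1.66 SD.
- ICC 0.05, k = 2: 6.25 / (1.125 + 0.048) = 5.3 df, t = 1.99, width = 1.34 SD.
- ICC 0.10: about 2.0 SD (k = 1) and 1.5 SD (k = 2).

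These are much wider than the 1.11 and 1.21 SD above, which treat the ICC as known.

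**The case against.** **The documents show no correlation.** This stands. No ICC, group size or number of groups is given. A reader might infer that the intervals are too narrow and that the 1 SD width is missed; the documents support only the conditional statement.

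**The width depends on drop-out.** This stands for the width. With all 30 per arm evaluable in two groups of 15, it stays within 1 SD up to an ICC of about 0.05. It does not restore coverage, which is then about 91% for a nominal 95% interval.

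**The model may be completed in a statistical analysis plan.** This stands in part. The article names a model class without its random effects, and a session-group effect would contradict nothing written, so its silence is not proof that the group will be ignored. The precision statement is different: it is fixed in the article on independence, and a later analysis plan does not change what that statement assumes.

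**Shared therapist and fixed groups are not stated.** This stands. The protocol speaks of therapists in the plural, and half of the AT sessions are guided visits to the gallery or museum. One might infer a single group per arm, because each art site hosts participants only once a month in the first three months and recruitment from 13 June 2016 to a trial end in April 2017 leaves little room for successive cohorts. This is suggestive, but settles nothing.

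**The error does not favour the intervention as such.** This stands. One might infer a bias towards benefit, but narrow two-sided intervals give false signals both ways. This is also a pilot on feasibility, with no success rule attached to the intervals.

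**Conclusion.** The point holds in conditional form. AT and MRA participants are treated in interacting groups, the 22 per group assumes independence, and the stated model names only repeated measurements. If outcomes correlate within session groups, the active-versus-control intervals under-cover in both directions, and the 1 SD width is not assured at 22 evaluable per arm.

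The size ranges from negligible (small groups, ICC near 0.01) to material (one or two large groups, ICC 0.05 to 0.10). Over the cases considered at 22 per arm, the true width runs from about 1.0 to 1.4 SD, and nominal 95% coverage falls from about 95% to 83%. These figures rest on assumed ICCs and group sizes, equal SDs across arms and normal quantiles. Point estimates and the randomization itself are not in question.

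**What to change.** 1. Record each active participant's session group and therapist, and state the number and size of groups.
2. In the sample size justification, say that the 1 SD width assumes independent participants. Give the range of about 1.0 to 1.4 SD at 22 per arm, with the ICCs and group sizes behind it.
3. Beside the planned model, report the active-versus-control intervals with the ICC fixed at 0.02, 0.05 and 0.10.
4. Fit a partially nested model (session-group random effect in AT and MRA only, small-sample degrees of freedom) only if each arm has enough groups to estimate the group variance.
5. If there is one group per arm, state that group and therapist effects cannot be separated from the intervention.

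The cost is two recorded variables, a few sentences and a short sensitivity analysis; no extra participants are asked for. The downside is wider, less favourable intervals. If the group variance is estimated from few groups they become much wider: about 1.3 to 1.7 SD with two groups of 11 and ICC 0.05.

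### The primary mixed model leaves the handling of baseline unstated and the stratification factor optional, which on its ordinary reading forgoes some precision

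*Protocol article*

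**What the plan says.** In the protocol article, Statistical analyses, the neuropsychological scores "at baseline, three months, and nine months will be modeled using the linear mixed model for repeated measurements". Baseline is therefore one of the responses. The quantities to be reported are "Differences in the estimated means of the changes at three and nine months from baseline between the intervention and control groups". Two interval levels are planned for each of these contrasts: "their associated 90% and 95% confidence intervals will be calculated". No baseline covariate is named, and nothing says whether the arms share a baseline mean.

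Covariates come in one further sentence: "Further, analysis may be performed to adjust the model for potential confounders, such as age, gender, and education level". Under Randomization procedure, participants are allocated "to the AT, MRA, or control groups at a 1:1:1 allocation ratio" by "permuted block randomization stratified by gender". The factor used to stratify is thus one of the examples in the optional analysis.

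Sample size justification is built on precision. The target is a full interval width of 1 SD, and the confidence level, contrast and time point follow from the description of an interval "which has a 90% chance to include the true difference of mean change in neuropsychological test score at three months". This leads to 22 per group, 30 after 25% drop-out, and 90 in all.

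**The concern.** Randomization makes the expected baseline means equal across arms. A model that gives each arm its own baseline mean ignores this, and the difference in change then inherits whatever baseline imbalance arose by chance. With about 22 evaluable participants per arm, that imbalance is not negligible. Precision is the criterion on which this pilot was sized, so giving some of it away matters even though no stated target is missed.

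The second part concerns specification. Gender was used to restrict the randomization, yet its place in the model is left to discretion, with an open-ended list of companions. In a randomized trial these variables are prognostic covariates and do not confound the comparison. If adjusted and unadjusted versions of several tests at two time points are both available, the plan should say beforehand which one is primary.

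**Working it through.** **Inputs.** From the protocol: 90% interval, full width 1 SD, 22 per group, 25% drop-out, 30 per group. The baseline to follow-up correlation r is not given, so I assume 0.5 to 0.9. I read the SD as the SD of change, and take equal score SDs at each visit unless stated.

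**The plan's own figure.** Setting 2 × 1.645 × SD × √(2/n) = 1 SD gives n = 8 × 1.645² = 21.6, so 22. Then 22/0.75 = 29.3, so 30, and 3 × 30 = 90. The figures reproduce, and they do so from the plain variance of change with no allowance for baseline adjustment. At n = 22 the width is 2 × 1.645 × √(2/22) = 0.992 SD. (With a t quantile on 42 degrees of freedom it is 1.014 SD; the plan evidently used the normal approximation.)

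**Effect of baseline adjustment.** With score variance s², the change variance is 2s²(1 − r) and the baseline-adjusted variance is s²(1 − r²). The variance ratio is (1 + r)/2 and the width ratio is √((1 + r)/2).

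| r (assumed) | Width ratio | 90% width at 22 per arm (SD of change) | n per arm for 1-SD width |
|---|---|---|---|
| 0.5 | 0.866 | 0.859 | 17 |
| 0.6 | 0.894 | 0.887 | 18 |
| 0.7 | 0.922 | 0.914 | 19 |
| 0.8 | 0.949 | 0.941 | 20 |
| 0.9 | 0.975 | 0.967 | 21 |

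The direction does not depend on equal SDs. With s0 at baseline and s1 at follow-up, change variance minus adjusted variance is (s0 − r·s1)², which is never negative.

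**The mixed model itself.** I took three visits, equal correlations, complete data and 22 per arm. At r = 0.7 the generalized least squares SE of the three-month change contrast is 0.2335 score SD with free baseline means, identical to the change-score SE. With a common baseline mean it is 0.2153, a ratio of 0.922. The ratios at r = 0.5 and 0.8 are 0.866 and 0.949, as in the table.

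**Small samples.** A simulation at 22 per arm with the slope estimated gave variance ratios of 0.76, 0.83, 0.86 and 0.93 for r = 0.5, 0.6, 0.7 and 0.8. Taking square roots, the intervals are about 13%, 9%, 7% and 4% narrower.

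**Drop-out.** Suppose 30 per arm have a baseline score and 22 have follow-up. The free-mean contrast then has variance 2s²[(1 − r²)/22 + (1 − r)²/30], because the model also uses the baselines of those who leave. The common-mean contrast has 2s²(1 − r²)/22. At r = 0.5 the SEs are 0.2913 and 0.2611 (ratio 0.896). At r = 0.8 they are 0.1881 and 0.1809 (ratio 0.962). The gain is then about 10% to 4%.

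**Chance imbalance.** The baseline difference between two arms of 22 has SD √(2/22) = 0.30 score SD. The change contrast carries (1 − r) of it: 0.15 at r = 0.5 and 0.06 at r = 0.8. Against adjusted SEs of 0.261 and 0.181, that is about 0.6 and 0.3 of an SE.

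**Gender.** With arms balanced on gender and residual variance fixed, adding gender as a main effect or by visit leaves the SE at 0.2335 (r = 0.7). A stable gender effect cancels in a change contrast. If gender explains a share R² of the variance of change, the width ratio in a two-arm change regression is √((1 − R²) × 42/41): 1.012 at R² = 0, 0.986 at 5% and 0.960 at 10%.

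**The case against.** The strongest reply is that the text does not compare raw changes. It reports model-estimated changes from a mixed model, and with a common baseline mean the same sentence would describe the better analysis. This stands in part: the loss is conditional on free baseline means, and with drop-out the free-mean model recovers some of it. But free arm means are the ordinary reading when no constraint is stated, and the sample size, built on the plain change variance, points the same way.

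A second reply is that such detail belongs in an analysis plan that is not shown. The protocol does, however, state its primary contrast and its policy on covariates, and both can be improved with data already collected.

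A third reply is that the adjustment sentence follows the main model and reads as supplementary, so the unadjusted model is already primary. That is a fair reading, and it weakens any suggestion that the plan invites picking a favourable model. The stratification factor still has no fixed place in the analysis.

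A reader might infer more: that omitting gender noticeably widens the intervals or misstates the SE, that the trial is undersized, or that the estimate is biased. The documents support none of these. A stable gender effect cancels, the sizing figures reproduce, and chance imbalance averages to zero over randomizations.

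**Conclusion.** The point holds as forgone efficiency and an incompletely fixed primary model. On the free-baseline reading, a baseline-adjusted analysis of the same data would give 90% intervals about 13% to 5% narrower for an assumed r of 0.5 to 0.8, and about 3% narrower at 0.9. The gain is slightly less once the slope is estimated, and about 10% to 4% over the 0.5 to 0.8 range if a quarter of participants contribute only a baseline score. The size rests on r, which the protocol does not give; the direction does not. The 1-SD target is met without adjustment on the plan's own approximation.

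For gender, the gain is consistency with the randomization and one less open choice. The width moves by roughly +1% to −4%, depending on whether gender predicts change.

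**What to change.** In Statistical analyses, state that the primary linear mixed model constrains the three randomized arms to a common baseline mean, with arm-by-visit terms after baseline and gender as a fixed effect. Make any adjustment for age and education a prespecified sensitivity analysis with the covariates listed, and report the unadjusted model as a further sensitivity analysis.

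The common-mean form is preferable to entering baseline as a covariate, because it keeps participants who have only a baseline score, in line with the protocol's rule that all randomized participants are analysed. The planned free-mean model keeps them too, so nothing is lost on that count.

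The cost is wording alone, settled before outcomes are examined by arm. Baseline scores and gender are already collected, and the sample size need not change.
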